### Blinding

Post-intervention measures will be administered by a pair of junior researchers (student SLTs at UCL) with skills in the assessment of people with PPA but crucially blinded to group allocation. Participants and family members will be asked not to reveal their allocation during the post-assessment session. They will be reminded of this prior to their appointment, by letter and verbally, at the start of the session. Should the students become unblinded during the reassessment process, this will be documented and the reasons recorded.

### Sample size justification

As there are no data available to estimate a sample size, the recruitment of participants has been dealt with pragmatically. Based on discussion with clinicians at the primary research site, it is estimated that it will be possible to recruit 42 participants over an 18-month period at seven sites. This pilot will provide information on recruitment and retention and facilitate a sample size calculation for a future full trial. Recruitment will be reviewed at 2-month intervals during the study, and the recruitment strategy will be amended as necessary to achieve the target number.

### Pre- and post-intervention measures

Participants will complete pre-intervention language, communication and quality of life measures (see Table 2) with the local collaborator in week 1 of the study. Completing assessment to gain an insight into areas of communication strength and difficulty prior to commencing intervention is routine procedure in speech and language therapy practice, and importantly, provides the opportunity for local collaborators to build rapport with participants before delivery of the intervention. All measures will be repeated after intervention at week 6 by a pair of junior researchers. In order to collect communication data, participants will be trained to independently use an iPad to video record conversation samples. A conversation topic list will be provided to support this process should they require it. Table 3 summarises the schedule of pre- and post-intervention measures.

**Table 2 Tab2:** List of pre- and post-intervention measures

Language measures: 1. Comprehensive Aphasia Test [43] This language battery provides a profile of performance across all modalities of language production and comprehension.	
Communication measure: 1. Video recordings of conversation samples This informal measure adapted from the Aphasia Conversation Measure [21] identifies barriers and facilitators to conversation between the person with PPA and their CP and assesses changes in conversation after intervention	
Quality of life measures: 1. Dementia Quality of Life Measure [44] This questionnaire is designed to ask people with dementia to rate their quality of life across the three main domains of feelings, memory and everyday life. 2. The Aphasia Impact Questionnaire [45] A tool designed to measure the impact of living with aphasia across three domains of communication, participation and emotional well-being. 3. Communication Confidence Rating Scale for Aphasia [42] This is a questionnaire of communication confidence that uses a self-rating scale designed for people with aphasia. 4. Perceived Stress Scale [46] (completed by CP only) This is a self-report questionnaire for measuring the respondent’s perception of stress. 5. Zarit burden interview [47] (completed by CP only) This is a caregiver self-report questionnaire for measuring personal and care strain.

**Table 3 Tab3:** Schedule of pre- and post-intervention measures

	Consent session			Preintervention assessment (1 week)	Treatment/control (4 weeks)				Postintervention assessment (1 week)				Final data collection
Week	0			1	2	3	4	5	6				7
Conversation	1a	2i	3i	4a					5a	6i	7i	8i	

Conversation video recording: a, assessor present but not in room; i, independent home recording

### Description of the intervention

#### BCPPA program

BCPPA provides a protocol for SLTs to deliver a four-session communication training program for people with PPA and their CPs. Participant's pre-intervention video-recorded conversation samples will be used to provide clips for video feedback during intervention sessions. The manual is made available to local collaborators online. The intervention is described in detail in Additional file 1, using the TIDieR checklist [28].

#### No speech and language therapy treatment

Those participants assigned to a no speech and language therapy treatment condition will receive usual healthcare provision (anticipated to include neurology, GP reviews, and allied health input such as physiotherapy). However, this will exclude speech and language therapy intervention for the duration of their participation in the study. The period of no speech and language therapy treatment will be 5 weeks – 4 weeks when the treatment group will receive BCPPA and 1 week when all participants complete post-intervention measures. As there is no critical period for treatment delivery for people with PPA, after this brief period, the participants allocated to the no speech and language therapy treatment group will resume all aspects of local speech and language therapy provision without further interruption.

### Training of local collaborators

Local collaborators will be trained to deliver the BCPPA program by the first author and will be provided with a training package including all required materials. Table 4 presents an overview of training content.

**Table 4 Tab4:** Overview of training of local collaborators (SLTs)

Training goals For local collaborators to be able to: • Identify potential participants who meet the study inclusion criteria • Consent participants to the study • Deliver the BCPPA program • Complete pre-intervention measures • Complete fidelity measures • Access the support and advice of the researcher (first author) throughout the study	
Pre-training work • Pre-reading materials from the Study Training Pack to support participant identification, completion of outcome measures and delivery of intervention	
Day 1. (4.5 h) • Overview study procedures. • Discuss inclusion/exclusion criteria with vignettes to problem solve • Discuss consent procedures and flow chart with accompanying case study. • Discuss purpose and process of video recording conversation samples as outcome measure and to support therapy • Practice video recording for conversation samples. • Observe sample video recordings and identify barriers and facilitators to conversation with a view to planning therapy	
Day 2. (4.5 h) • Discuss and practice completing remaining outcome measures • Discuss therapy sessions with practical role play tasks, practice completing session plans, and observe sample video recordings demonstrating delivery of intervention, including goal setting and having emotional conversations. • Discuss fidelity measures (video recordings, local collaborator adherence questionnaire, and participant feedback questionnaires) • Provide contact information for ongoing support	

### Assessment of treatment fidelity

In order to ensure treatment fidelity, each local collaborator’s sessions with their first participant will be observed by the first author (via remote viewing of a video recording) and feedback will be provided over Skype or by telephone. After that, telephone and email support will occur as needed, to ensure knowledge and skills are maintained. In addition, to ensure adherence is maintained, local collaborators will be asked to audio record the intervention sessions with all participants. A random sample of 10% of recordings will be analysed using a treatment adherence checklist by two independent raters to permit an investigation of inter-rater reliability. A further 10% of this random sample will be analysed by a second rater, and any differences will be discussed and agreed. Local collaborators will also be asked to reflect on adherence by completing an adherence questionnaire and by documenting session length and tasks completed. These will be anonymously returned to the first author in pre-stamped addressed envelopes.

### Assessment of acceptability of the intervention

In order to ensure the treatment is acceptable to people with PPA, their CPs and local collaborators, each will be asked to provide feedback on the intervention. Accessible feedback forms will be given to participants with PPA and their CPs at every intervention session, to be completed and returned anonymously in pre-stamped addressed envelopes directly to the first author. Additionally, local collaborators will be asked to include feedback on acceptability as part of the adherence questionnaire, completed after every session.

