**Methods:**

A single blind, randomised controlled pilot study will recruit 42 participants with primary progressive aphasia and their conversation partners across seven UK National Health Service Trusts. Participants will be randomised on a 1:1 basis, stratified by site, to receive either the ‘Better Conversations with Primary Progressive Aphasia’ intervention (21 couples) or no speech and language therapy treatment (21 couples). Participants are recruited by SLTs who will conduct pre-intervention assessment (week 1) and deliver the intervention (weeks 2 to 5). Junior researchers, who are blinded to allocation, will complete post-intervention measures (week 6). SLTs complete 9 h of training to prepare them to deliver the intervention. The primary objective of the study is to establish for a phase III effectiveness study whether the program can be delivered as intended in a UK National Health Service setting. Specifically, it will establish (1) the acceptability of randomisation, (2) an assessment of treatment fidelity to determine necessary levels of SLT training, (3) the most appropriate primary outcome measure, (4) sample size requirements, (5) predicted patient recruitment and retention rates and (6) refined inclusion criteria.

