Analysis of fidelity and adherence data will inform future training needs. Although fidelity data is sparse for speech and language intervention trials, processes such as those deployed in our study have been shown to achieve an average of 80–100% fidelity [37–39]. Thus, we have selected 80% as the minimum target for fidelity. Acceptability of the intervention will be considered, based on analysis of the participant feedback forms and adherence data to inform further refinements of the intervention prior to a future full trial. Analysis of participant feedback and adherence data will use descriptive statistics. For open-ended questions or ‘other’ response categories, qualitative analysis will be used, specifically identifying themes and sub-themes using thematic analysis [40].

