### Criteria for success

This study will be considered appropriate to proceed to a full trial if:▸Patients and local collaborators report generally positive views about acceptability of randomisation and of intervention as determined by evaluation of feedback forms;▸A suitable sensitive outcome measure is determined and sample size estimated;▸Local collaborator intervention-fidelity rate is at least 80%.

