### Assessment and management of risk

This is a low-risk study. It is possible that participants will not experience improvements as a result of the intervention. However, there is evidence to suggest that such interventions are effective for improving communication and well-being in adults with non-progressive aphasia and their carers [14]. Importantly, there is no evidence to indicate that participants will experience any harmful effects. Most of the measures used in this study are frequently used in routine clinical practice with people with PPA. Additionally, the local collaborators are SLTs with skills to complete measures in a sensitive and supportive manner, minimising risk of distress. If participants do not feel emotionally or physically well enough to continue, then an assessment will be postponed. Video recording of conversations might also cause distress. To minimise the risk, we will ensure that as far as possible, the participants are familiarised with recording devices and understand why video recording is necessary. All procedures are set out within our participant information sheets (see Additional file 1) and consent forms, which were co-produced with the study steering group of people with PPA and their carers. Participants will be reminded that they can withdraw from the study at any time without giving a reason. Any adverse events will be recorded in the participant’s medical record, and the study sponsor informed.

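### Acceptability of BCPPA is gathered only from sources tied to delivered sessions, and the go criterion ignores attrition, so couples who stop are under-represented

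*Protocol article*

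**What the plan says.** All references are to the protocol article.

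- **Size and dose.** The Abstract (Methods) allocates couples to the "intervention (21 couples) or no speech and language therapy treatment (21 couples"). The section BCPPA program describes "a four-session communication training program for people with PPA and their CPs".
- **Participants' views.** Under Assessment of acceptability of the intervention, "Accessible feedback forms will be given to participants with PPA and their CPs at every intervention session". On how the forms come back, that section says they are "to be completed and returned anonymously in pre-stamped addressed envelopes directly to the first author".
- **Therapists' views.** The same section adds that "local collaborators will be asked to include feedback on acceptability as part of the adherence questionnaire, completed after every session".
- **Analysis.** Data analysis states: "Acceptability of the intervention will be considered, based on analysis of the participant feedback forms and adherence data". It also plans descriptive reporting of attendance, attrition and reasons for dropout.
- **Decision.** The first of the three conditions under Criteria for success is: "Patients and local collaborators report generally positive views about acceptability of randomisation and of intervention as determined by evaluation of feedback forms". The other two concern an outcome measure with a sample size, and fidelity of at least 80%.
- **Withdrawal.** Under Assessment and management of risk, "Participants will be reminded that they can withdraw from the study at any time without giving a reason".

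The article describes no acceptability form at withdrawal, at the end of treatment or at follow-up.

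**The concern.** Every source named for the acceptability of BCPPA arises from a session that took place: the participant form, the therapist questionnaire and the adherence data. A couple's chance to be heard therefore falls with each session not attended, and a couple that stops before the first session is not heard at all. Stopping can itself express low acceptability, so the missing views may depend on the very answer being sought.

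Nothing in the decision rule offsets this. None of the three conditions looks at how many BCPPA couples stopped or why. Retention feeds the sample size of the future trial, but not the judgement on acceptability. Fidelity is likewise rated from recordings of sessions that were delivered. All three conditions could be met while a part of the arm had left because it disliked the program.

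The gap lies in data collection, so an analysis plan cannot fully close it. Views not sought after stopping cannot be recovered. With anonymous return as described, forms also cannot be re-weighted by couple, nor can those from couples who stopped be picked out.

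**Working it through.** The article gives no acceptability figure, dropout rate or threshold, so there is no stated number to reproduce. The check counts how much of the evidence can come from couples who stop.

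**Inputs from the article:** 21 couples in the BCPPA arm; 4 sessions; one set of forms per couple per attended session. The maximum is 21 × 4 = 84 form sets, or 168 individual forms if both partners return one. Counting by person leaves the shares below unchanged.

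**Assumptions, not in the article:** d couples stop after k sessions, all others attend all four, and every form is returned.

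**Formula:** share of form sets from couples who stop = d·k / [(21 − d)·4 + d·k].

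| Couples stopping (share of arm) | Before session 1 | After session 1 | After session 2 | After session 3 |
|---|---|---|---|---|
| 2 (9.5%) | 0/76 = 0% | 2/78 = 2.6% | 4/80 = 5.0% | 6/82 = 7.3% |
| 4 (19.0%) | 0/68 = 0% | 4/72 = 5.6% | 8/76 = 10.5% | 12/80 = 15.0% |
| 6 (28.6%) | 0/60 = 0% | 6/66 = 9.1% | 12/72 = 16.7% | 18/78 = 23.1% |

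The share of forms is always below the share of couples. The gap is widest for early stopping and small for late stopping.

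**What this could do to a summary.** This step needs two further assumptions: that forms are simply pooled, and that 90% of views are positive among completers and 20% among couples who stop.

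- 4 couples stop after session 1. Pooled forms: (68 × 0.9 + 4 × 0.2)/72 = 62.0/72 = 86.1%. One result per couple: (17 × 0.9 + 4 × 0.2)/21 = 16.1/21 = 76.7%.
- 6 couples stop after session 1. Pooled forms: (60 × 0.9 + 6 × 0.2)/66 = 55.2/66 = 83.6%. One result per couple: (15 × 0.9 + 6 × 0.2)/21 = 14.7/21 = 70.0%.
- If those couples never attend, the pooled figure stays at 90.0% however many are lost.

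These figures show direction and rough scale under the stated assumptions. They do not predict what the pilot would report.

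**The case against.** Several points on the other side have force.

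- **Couples who stop are not wholly silent.** They can return forms for the sessions they attended. As return is by post, a form may be filled in after the decision to stop and may record the dissatisfaction. The therapist also reports on those sessions. This stands: the right description is under-represented, and unheard after stopping.
- **Attrition will be visible.** Data analysis commits to reporting it with reasons, and retention is a stated aim, so a reader of the results would see the loss. Participants need not give a reason, but that does not prevent reasons being given. This also stands. What remains is that the decision rule does not use the information.
- **No pooling rule is stated.** A reader might infer a large distortion. For example, suppose 5 dissatisfied couples stop after session 1 and 16 satisfied couples complete. Of 5 + 16 × 4 = 69 form sets, 64 (92.8%) would then be positive, against 16 of 21 couples (76.2%). The documents do not support that reading. They give no dropout rate, do not say that forms are pooled into a percentage, and also plan thematic analysis of open answers.
- **No wrong decision is shown.** The criterion has no numerical threshold, and couple-level figures of 70% to 77% might still be called generally positive. This is correct, and it limits the claim to a tilt in the evidence.
- **The article condenses a fuller protocol.** Weighting and unit of analysis may be settled there. The article does, however, fix when views are collected and what the criterion rests on. If the full protocol already contains an exit form, the collection part of this point falls away.

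**Conclusion.** The point holds in a limited form. As the article stands, evidence on the acceptability of BCPPA comes only from delivered sessions, and the go criterion is decided on feedback forms without the attendance, attrition and dropout reasons that will be available. Couples who stop carry less weight than their number warrants, and none if they never start. The criterion leans towards acceptable provided that couples who stop are less satisfied than those who finish. That is plausible, but the article does not establish it.

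The size cannot be fixed. Across 2 to 6 couples stopping after session 1, with full return, 9.5% to 28.6% of couples would supply 2.6% to 9.1% of form sets; with later stopping the gap narrows. It does not follow that the pilot would hide a failing intervention, because attrition is to be reported. This is a weakness in a stated decision rule that is cheap to repair before the decision is made.

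**What to change.** 1. **Assessment of acceptability of the intervention.** Offer each randomised BCPPA couple one short acceptability form, either at the week-7 final data collection already in the schedule or by post when they stop. Return it as now, marked only as completed or stopped early. No study number is needed, so anonymity is kept. Keep it away from the blinded week-6 assessors. Continue the session forms.
2. **Criteria for success.** Judge acceptability of the intervention with all randomised BCPPA couples as the denominator, read alongside attendance, attrition and reasons for dropout. Count couples who gave dissatisfaction as their reason for stopping as not acceptable. Show the result twice for couples who stopped without a form or a reason: once counted as not acceptable and once left out. Some will have stopped for unrelated reasons, so the two results give a range and neither should stand alone.

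Because the forms are unlinked, a reason recorded at site cannot be matched to a returned form. Asking for the reason on the form itself limits double counting.

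The cost is one extra short form for up to 21 couples, a sentence in each of the two sections, and possibly a less favourable acceptability figure.

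### Acceptability of randomisation is a go condition read from feedback forms, but the forms described reach only couples allocated to therapy, so control couples have no described route into the patient side

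*Protocol article*

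**What the plan says.** The Aim section of the protocol article lists acceptability of randomisation first among the things the pilot is to establish. Criteria for success turns it into a condition for a full trial: "Patients and local collaborators report generally positive views about acceptability of randomisation and of intervention as determined by evaluation of feedback forms". That sentence names the respondents (patients and local collaborators) and the data source (feedback forms).

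The forms are described under Assessment of acceptability of the intervention. People with PPA, their conversation partners and the collaborators are covered, and "each will be asked to provide feedback on the intervention". For participants, "Accessible feedback forms will be given to participants with PPA and their CPs at every intervention session". For the therapists, "local collaborators will be asked to include feedback on acceptability as part of the adherence questionnaire, completed after every session". The article states no other hand-out point and does not say that either instrument asks about randomisation.

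On the control arm, the section No speech and language therapy treatment says that usual healthcare continues but "this will exclude speech and language therapy intervention for the duration of their participation in the study". The abstract gives the allocation: "Participants will be randomised on a 1:1 basis, stratified by site", with 21 couples in each arm.

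**The concern.** Randomisation is tested most severely in the people who draw the less attractive arm. The Background describes people with PPA as commonly keen to obtain speech and language therapy, and the Discussion counts the untreated control period among the limitations. Control couples are therefore the group whose opinion of randomisation the planners of a full trial most need. If forms are given out only where therapy is delivered, that group is not asked.

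What is at stake is one part of the progression decision and the first aim. A criterion that cannot register dissatisfaction in the control arm could be met while a serious recruitment or retention problem for the full trial goes unseen. The Data analysis section also uses participant feedback forms to shape future recruitment procedures, so the same gap would carry into the planning of the next trial.

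**Working it through.** The article has no figure to reproduce here. The sample size of 42 is pragmatic and plays no part beyond the arm split. The check is a cross-reading followed by a count.

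**Statements side by side**

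| Step | Where in the protocol article | What it gives |
|---|---|---|
| Aim | Aim | Acceptability of randomisation, listed first |
| Go condition | Criteria for success | Views on randomisation and intervention, read from feedback forms |
| Participant forms | Assessment of acceptability of the intervention | Given at each intervention session; subject is the intervention |
| Collaborator feedback | Same section | Inside the adherence questionnaire, after each session |
| Control arm | No speech and language therapy treatment | No such therapy while in the study, hence no intervention sessions |

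Table 4 (training of local collaborators) lists participant feedback questionnaires among the fidelity measures, which agrees with their being attached to therapy delivery.

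**Count of forms**

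Inputs: 21 couples per arm (abstract), four sessions (BCPPA program) and, as an assumption, one form each for the person with PPA and the conversation partner.

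- BCPPA arm, maximum: 21 × 4 × 2 = 168 forms from 21 couples.
- Control arm: 21 × 0 = 0 forms.
- Couples with a described route: 21 / 42 = 50%.

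**What the forms can and cannot show**

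Let pT and pC be the shares of treated and control couples who find randomisation acceptable. With 1:1 allocation, the share among all couples is 0.5 × pT + 0.5 × pC, while the forms estimate pT alone. The difference, forms minus truth, is 0.5 × (pT − pC).

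- If pT = 100%, the overall share runs from 0.5 × 100% + 0.5 × 0% = 50% to 0.5 × 100% + 0.5 × 100% = 100%. The forms read 100% throughout.
- If pT = 90% (assumed), the overall share runs from 45% (pC = 0%) to 95% (pC = 100%). At an assumed pC of 50% it is 45% + 25% = 70%, and the forms still read 90%.

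The values of pT and pC are illustrations; the article gives none. The sign of the difference depends on whether control couples are less or more content than treated couples.

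**With a form to both arms**

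Couples able to report rise from 21 of 42 (50%) to 42 of 42 (100%), before dropout.

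**The case against.** The strongest reply is that the article is a condensed account. The section on acceptability is about the intervention, so it naturally describes hand-out at sessions, and it does not say that these are the study's only forms. The participant flowchart is not shown, the additional files are not at hand, and Table 3 has a week-7 final data collection column whose content is not given. This stands to the extent that a reader might infer that no control-arm form exists anywhere, which the article does not establish. It does not remove the point. The article itself states the criterion, its data source and the hand-out point, and these do not fit together as written.

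A second reply is that other evidence bears on aim 1. Under Identification and recruitment of participants, a log records eligible people who decline and their reasons if given. Under Data analysis, attrition and reasons for dropout are reported. Both are useful, but neither is named in the criterion. Decliners were never randomised, and participants may withdraw without explanation. A control couple who is unhappy with allocation but stays in the study appears in neither source.

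A third reply is that collaborators also count in the criterion. They recruit, consent and assess couples in both arms and are told each allocation. That is correct and limits the point to the patient side. Their questionnaire is nonetheless completed per session, so nothing described prompts them about the control arm.

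**Conclusion.** The point holds in this form: as described, 21 of 42 randomised couples (50%) have no route into the patient side of the randomisation criterion, which therefore cannot reflect the views of couples allocated to no speech and language therapy. It is also not stated that treated couples are asked about randomisation, since the forms are described as feedback on the intervention. The conclusion rests on the planned 21:21 split and on the stated hand-out point being the only one.

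Three stronger readings are tempting and are not supported.

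- A reader might infer that treated couples alone decide whether a full trial proceeds. Collaborators' views count in the same criterion, and two further conditions (a suitable outcome measure with a sample size estimate, and fidelity of at least 80%) must also be met.
- A reader might infer that the criterion is bound to look favourable. Treated couples or collaborators may report negative views. What can be said is that the result will not respond to control couples' opinions.
- A reader might infer from the anonymous return of forms that responses cannot be linked to couples and that losses go unseen. Data management puts a unique participant number on paperwork, which may cover these forms, and dropout is recorded. Anonymous return is a trade-off with candour and a separate matter.

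**What to change.** Give every couple in both arms one short form on randomisation and allocation at a common point after allocation. Posting it around week 6, for return directly to the research team, keeps it out of the hands of the blinded assessors. Post the same form to couples who withdraw, if they agree, since they may not attend the week-6 visit. Ask collaborators explicitly about randomisation across both arms, separately from the per-session adherence questionnaire.

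Report acceptability of randomisation by arm. Reword Criteria for success so that its randomisation part rests on both arms and is read alongside the decliner log and dropout reasons by arm. If a control-arm form already exists, one sentence saying who receives it, when, and that it asks about randomisation would close the gap in the text.

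The cost is one additional short form per couple, one extra question set for collaborators and a minor amendment.
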